#### Recruitment

Patients will be given the opportunity to either participate in this trial or not. However, each clinical centre is within a hospital where a wide spectrum of patients with severe somatic conditions are treated and would give us the ideal platform to recruit participants.

### Randomisation

#### Sequence generation & allocation concealment

Participants are randomly assigned following randomisation procedures to either the intervention group or the control group. Block randomisation is used to ensure an equal number of patients in the intervention and control group at each site. The block randomisation randomizes patients in the control and treatment group in blocks of size ten. This is necessary as each clinical centre treats different somatic conditions, and these should be equally distributed between the two groups. Randomisation is centralized and carried out by an electronic system developed by UPM (Universidad Politécnica de Madrid) in collaboration with KI (Karolinska Institutet). This is done to conceal the randomisation from the researchers involved in enrolment and assessment.

Once the patient has met the eligibility criteria and is enrolled in the study, he/she will complete the baseline assessment. The clinician will then connect to a web page and obtain a randomly generated code to be assigned to the patient. The patient will be assigned to either the control group or the intervention group according to the code.

#### Blinding

Blinding of patients and treating physicians to treatment allocation is not possible. The clinical psychologists who evaluate the patients at baseline and the two follow-up assessments are, however, different from those who randomise and allocate the patients to either the intervention or control group as well as provide the intervention group about the NEVERMIND system. All evaluators are blinded to the group allocation. Any incidence of unblinding is reported to and recorded by the respective centres.

#### Statistical analysis

Intention-to-treat (ITT) analysis will be carried out, which hypothesises the superiority of the NEVERMIND system in reducing depressive symptoms in comparison to TAU. A linear mixed model will be used in order to use all available data of each subject and choose an appropriate covariance structure reflecting the potential dependence due to repeated measures. In order to account for the repeated measurements, the baseline measures will be adjusted for in the model [30, 34]. This increases statistical power, accounts for regression towards the mean, and has been recommended for longitudinal analysis of RCTs [35, 36]. Therefore, the ITT for the primary outcome (BDI-II score at 12-weeks) will be used as recommended for statistical analysis of clinical trials by the European Medicines Agency (EMA; codes CPMP/ ICH/363/96 and CPMP/EWP/2863/99). Group (intervention and control), disease type, and hospital will be included as fixed factors.

Comparison of demographic and clinical characteristics at baseline between subjects of varying primary somatic conditions and clusters as well as between intervention and control group will be examined. In case of imbalances of some characteristics, explorative sub-group analyses will be performed.

If a difference between ITT and per-protocol analysis is observed, more weight will be given to the ITT analysis, which is seen as the primary analysis. If the NEVERMIND system does not show superiority effect over treatment as usual for the ITT analysis, we will look at the extent of usage of the different components of the NEVERMIND system. Additionally, secondary analyses of the primary outcome will include per-protocol evaluations and examine the preventive effect of the NEVERMIND system on the incidence of depression (sensitivity analysis). Analyses of the other secondary outcomes (quality of life, perceived stigma and self-efficacy) will be examined in a similar manner.

Loss to follow-up will be handled through multiple imputations [37] if the missingness is below the recommended rate of missingness and the data structure allows for it as recommended by Jakobsen and colleagues [37]. Otherwise, inverse probability weighting [38] will be utilized. In case of loss to follow-up, observations are only imputed for missing outcomes at 24-weeks (12-weeks after the end of the intervention) by imputing the observation recorded at 12-weeks. No imputation will be performed for the primary outcome at the primary endpoint (T12). Sensitivity analyses will be conducted to test the robustness of the results by conducting complete-case and last observation carried forward analyses [30, 34, 35]. If a loss to follow-up occurs after one follow-up (at 12-weeks), the last observation will be carried out to subsequent follow-ups (from 12-weeks to 24-weeks).

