#### Secondary outcomes

Secondary outcomes to be measured include general well-being, patient self-efficacy management of primary somatic condition, perceived stigma, prevention of depressive symptoms, and sustainability of the effect of NEVERMIND at 24-weeks post-baseline assessment.

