#### Sample size

The NEVERMIND system was newly developed and is tested in this study for the first time. Therefore, we could not base the sample size calculations on a previously measured effect size. We estimated the sample size based on a previous study that evaluated the effectiveness of Deprexis in reducing depressive symptoms among patients with somatic disorders [30]. A very similar effect size was also found in a meta-analysis that looked at the effectiveness of Deprexis for depressive symptoms in different settings [18]. The sample size was calculated to detect a similar reduction in depressive symptoms (d = 0.54), where a linear mixed model analysis will be used with a power of 80%, two groups, an intercorrelation coefficient of 0.5 and a significance level of 0.05 (sistas-package [31] and lme4-package [32] for the primary outcome. According to power calculations performed with R [33] for the proposed linear mixed model analysis, 110 patients were estimated. Based on the recruitment criteria, which do not stipulate depressive symptoms as an inclusion criterium, we acknowledge that not all patients will exhibit depressive symptoms at recruitment. Therefore, the sample size was adjusted to account for this. We assume that at least 1/3 of the subjects in the sample of patients with chronic conditions will have depressive symptoms at baseline. In order to reach the desired sample size of 110 patients with depression or depressive symptoms, a sample of 330 subjects who complete the study is required to have adequate power to detect medium effects. A drop-out rate of 20% has been accounted for by adjusting the recruitment process.

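### The missing-data rules conflict, and carrying the 12-week score into week 24 biases the sustainability outcome towards a lasting effect if the effect fades

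*Protocol article*

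**What the plan says.** All the missing-data rules stand in the last paragraph of the protocol article's Statistical analysis section.

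- The general rule is: "Loss to follow-up will be handled through multiple imputations [37] if the missingness is below the recommended rate of missingness". A further condition is that the structure of the data permits it. Otherwise inverse probability weighting is used.
- The next rule narrows this for patients who drop out: "observations are only imputed for missing outcomes at 24-weeks (12-weeks after the end of the intervention) by imputing the observation recorded at 12-weeks".
- For the primary outcome: "No imputation will be performed for the primary outcome at the primary endpoint (T12".
- Robustness is to be tested by "conducting complete-case and last observation carried forward analyses". The closing sentence describes carry-forward as running from week 12 to week 24.

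Earlier in the same section, the main model is a baseline-adjusted linear mixed model that uses every available observation. The Intervention group section gives patients the system for 12 weeks. The Secondary outcomes section lists "sustainability of the effect of NEVERMIND at 24-weeks post-baseline assessment".

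**The concern.** There are two linked problems.

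First, the rules do not fit together. If the 12-week outcome is never imputed and the only imputation at week 24 is the week-12 score, the multiple imputation announced at the start of the paragraph has no missing outcome to fill. A statistician could defend at least three main analyses from this text: multiple imputation or weighting, observed data at week 12 with carry-forward at week 24, or the mixed model alone. That choice should not stay open until the data are seen, and it reaches the primary endpoint.

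Second, the sustainability outcome asks whether a benefit outlasts the system. A patient who leaves after week 12 has no off-system score. Carry-forward supplies an end-of-intervention score in its place, and so assumes for that patient what the outcome is meant to test.

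**Working it through.** **Which rule covers which visit**

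| Rule | Week 12 | Week 24 |
|---|---|---|
| Multiple imputation | excluded by the no-imputation sentence | excluded, because the only imputation is the week-12 score |
| Inverse probability weighting | compatible, since it imputes nothing | hard to combine with filled-in scores |
| Carry-forward | described only from week 12 onwards, so no change | fills the gap |
| Mixed model on available data | compatible | needs no filled-in scores |

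**Inputs**

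From the Sample size section: "The sample size was calculated to detect a similar reduction in depressive symptoms (d = 0.54"; "a power of 80%, two groups, an intercorrelation coefficient of 0.5 and a significance level of 0.05"; "for the proposed linear mixed model analysis, 110 patients were estimated"; at least one third of patients symptomatic at baseline; 330 patients; 20% drop-out. The split of drop-out before and after week 12 is not given.

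**The plan's own figure**

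For a two-sided test, n per arm = 2 × (1.96 + 0.842)² / 0.54² = 53.8, so 54 per arm and 108 in total. The t-test version gives 54.8, so 55 per arm and 110 in total, which is the stated figure. Then 110 × 3 = 330.

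**Bias from carry-forward**

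Let m be the share of analysed week-24 scores that are carried forward, and d12 and d24 the true effects. With drop-out unrelated to outcome:

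estimate = (1 − m) × d24 + m × d12, so bias = m × (d12 − d24).

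If d12 = d24 the bias is zero. If d12 = 0.54 and d24 = 0, the bias is 0.027, 0.054, 0.108 and 0.162 SD for m = 5%, 10%, 20% and 30%. If half the effect remains (d24 = 0.27) and m = 20%, it is 0.054 SD.

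**False claim of a lasting benefit when d24 = 0**

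SE = 2/√330 = 0.110. With adjustment for a baseline correlation of 0.5 (taking the plan's coefficient in that sense), SE = 0.110 × √0.75 = 0.095. The one-sided rate is P(Z > 1.96 − bias/SE), nominally 2.5%. The value 0.18 is 0.54/3, on the assumption that only the symptomatic third benefits.

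| d12 | m | Bias (SD) | Rate, unadjusted | Rate, adjusted |
|---|---|---|---|---|
| 0.54 | 20% | 0.108 | P(Z > 0.979) = 16.4% | P(Z > 0.827) = 20.4% |
| 0.54 | 10% | 0.054 | 7.1% | 8.2% |
| 0.18 | 20% | 0.036 | 5.1% | 5.7% |
| 0.18 | 10% | 0.018 | 3.6% | 3.8% |

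**Simulation check**

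Each scenario had 4,000 trials of 330 patients, correlation 0.5, baseline-adjusted regression at each visit and drop-out completely at random. Rates here are two-sided, nominally 5%.

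- d12 = 0.54, d24 = 0, all 20% lost after week 12: carry-forward estimates 0.108 and rejects 19.6%. Observed week-24 data estimate 0.00 and reject 4.8%.
- The same effects, with the 20% loss split evenly around week 12: carry-forward estimates 0.06 and rejects 8.6%. Observed data reject 4.6%.
- d12 = 0.18, d24 = 0: carry-forward rejects 6.1% to 6.6%.

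**What the sensitivity analyses add, if carry-forward is the main week-24 rule**

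- Week 24, carry-forward: the same rule as the main analysis.
- Week 24, complete-case: a real alternative, giving 0.00 against 0.06 to 0.11 when the true effect is zero.
- Week 12, carry-forward: the week-12 data are unchanged.
- Week 12, complete-case: the same week-12 records if it means week-12 completers. If it requires both visits, some records go, but the mean estimate stayed at 0.54 in the simulation.

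**The case against.** The strongest reply is that the carry-forward reading is only one reading. If multiple imputation or weighting is the main method, as the paragraph's opening says, carry-forward is merely a sensitivity analysis and neither sensitivity analysis repeats the main one. This stands, and it is why the first part of the point is the ambiguity and the second part is conditional on the reading.

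The size also depends on unfavourable inputs. The 20% drop-out is an overall figure, d = 0.54 was attached to 110 symptomatic patients rather than all 330, and complete loss of the effect is the extreme case. This stands too, so the result is given as a range. In addition, the outcome is secondary, and the Limitations section calls the trial a pilot and proof of concept. That limits the consequence but does not resolve the conflict, which also touches week 12.

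A reader might infer more than the text supports:

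- *That both sensitivity analyses merely repeat the main analysis.* They do not at week 24, where complete-case would expose the bias described here.
- *That week 12 has no protection against selective drop-out.* The mixed model allows for missingness that depends on observed data, and weighting is compatible with not imputing. What the stated analyses do not do is test departures from missing at random.
- *That patients who die would be given scores.* The rule speaks of loss to follow-up and does not say that deaths count as such. Their handling may be left to the analysis plan.
- *That the week-24 standard error is understated.* No calculation here shows by how much, and the point does not need it.

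**Conclusion.** The point holds in two parts. The missing-data rules contradict each other as written: multiple imputation is announced, and the following sentences leave it no outcome to impute. Separately, carry-forward is unsuitable as the main week-24 rule for an outcome about lasting benefit.

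The bias is conditional. With a stable effect and non-informative drop-out, the mean contrast is unbiased. With a fading effect, the error favours a lasting effect. It reaches 0.11 SD, with a one-sided false-positive rate of 16-20%, only if 20% of scores are carried forward, the effect vanishes by week 24 and d = 0.54 applies to all 330 patients. Under milder inputs the rate is 7-8% (10% carried forward) or about 4-6% (effect confined to the symptomatic third). The documents do not give the share carried forward or the degree of fading.

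If carry-forward is the main rule, repeating it as a sensitivity analysis adds nothing at week 24, and neither sensitivity analysis materially changes the week-12 data. Complete-case at week 24 remains a useful check.

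**What to change.** Rewrite the missing-data paragraph as follows.

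- Name one main method for both visits: the baseline-adjusted linear mixed model already specified, fitted to all observed BDI-II scores under missing at random.
- Delete carry-forward as the week-24 rule.
- Remove the switch between multiple imputation and inverse probability weighting as the main method.
- Replace the carry-forward sensitivity analysis with one that varies the missing-at-random assumption at weeks 12 and 24, for example delta-adjusted or control-based multiple imputation. Complete-case may stay.

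The cost is one rewritten paragraph, some added programming and a slightly wider week-24 interval. No extra patients or visits are needed.

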#### Data monitoring

The trial does not have a data monitoring committee (DMC) as the study leaders at each centre oversee each of their respective centres, while the project coordinator manages both the scientific and administrative aspects of NEVERMIND without a need of a DMC. Furthermore, the NEVERMIND centre at KI is responsible for the design and the coordination of the RCT, but each centre is responsible for overseeing data collection at their respective centre. However, there is an external review board that oversees the procedures of the trial. The study leaders will communicate regularly with the other members as well as the project coordinator regarding data collection, and the project coordinator ensures smooth internal and external communications. There are no plans to conduct an interim analysis.

#### Potential risks and harms

The risks associated with using the NEVERMIND application are minimal. If participants exceed a certain threshold in terms of depressive symptoms, anxiety, or suicidal ideation while using the application, they are immediately and automatically referred to a Case Manager (CM), which is a dedicated mental health worker employed at the clinical department where the NEVERMIND system is used. The CM will conduct several evaluations and refer the patient to a healthcare provider if a referral is needed. The CM will periodically contact the patient to monitor the effectiveness of the referral for up to six months.

### Trial status

The trial began enrolment in December 2017. Recruitment will be completed by March 2020. The trial has been registered on 23 November 2017 (DRKS00013391). [https://www.drks.de/drks_web/navigate.do?navigationId=trial.HTML&TRIAL_ID=DRKS00013391].

## Discussion

Despite the high prevalence of depression among patients with severe somatic conditions, there are very few interventions available to treat comorbid depression and none, to our knowledge, to prevent depression in these patients. The present study will provide evidence of whether the NEVERMIND system is an effective intervention in treating depression. If proven effective, the NEVERMIND system will significantly reduce the excess encumbrance posed by comorbid mental ill-health in patients with severe somatic conditions.

Firstly, the burden of disease felt by the patient would decrease, as they will now have the tools to help prevent mental health problems from occurring and will also be able to treat any depressive symptoms if they arise. The NEVERMIND system also provides guidance for lifestyle modifications required by the primary somatic condition, which may not be straightforward. This empowerment helps patients by providing a sense of control over their mental and physical health. Moreover, it can result in a perceived decreased burden for caregivers and the healthcare system. Patients using the NEVERMIND system do not need to rely on their caregivers as much, for they have a guidance system they can use instead of placing the demand on the caregiver. The NEVERMIND system also acts as a support system to primary healthcare, resulting in reduced health care visits as the overall health of the patient will improve.

Furthermore, the NEVERMIND system is a novel and innovative technology that has the ability to influence the use of technology in healthcare, as the system could in the future be adapted and used in many different settings. The system could be expanded to include a range of other conditions that have a high prevalence of depressive symptoms such as other cancers including pancreatic cancer or lung cancer, where the prevalence of depressive symptoms is estimated between 33 and 50% for pancreatic cancer [39] and between 11 and 44% for lung cancer. The system could also be adapted to include other conditions such as Human Immunodeficiency Virus (HIV), where depression prevalence is estimated between 22 and 45% [40]. In addition to using NEVERMIND for other conditions with a high prevalence of depression or depressive symptoms, the central machine learning could be adapted to be used in other contexts, such as in a holistic approach to the treatment of obesity or as a healthy weight management system. There is also the potential to develop the system so it can be available on different platforms such as converting the user interface to a smartwatch application or an application on tablet computers.

### Limitations

This RCT is designed as a pilot study to assess the NEVERMIND system as a proof of concept of its effectiveness, and the methods and study plan have several limitations. First and foremost, patients with and without the same primary conditions are recruited in different centres where the TAU is not consistent. This puts a limitation on the results of the effectiveness of the NEVERMIND system as we do not have a standardized control group. Secondly, there is an implication for cluster confounding. We will adjust the analyses for recruitment centre, but the recruited sample does not allow us to stratify the sample by somatic condition, country or clinic of recruitment. Another limitation was the method used to assess the ability to use Smartphone technology in the intervention group. This was assessed by asking patients if they were able to check and send emails using a smartphone, and not through a validated questionnaire. The inability of some patients to use the NEVERMIND might have an influence on the extent of its effectiveness. Similarly, patients who have been part of a pharmacological trial in the past were excluded with the intention of looking at the full effect of the NEVERMIND system without contamination. However, this might have excessively restricted the inclusion criteria. Thirdly, complete blinding is not achievable in this study. Even if different evaluators have been allocated to different groups of patients, we cannot ensure that incidents of unblinding do not happen. However, all incidents of unblinding are being recorded and will be reported with the results of the study. Lastly, the authors acknowledge that the results of this trial will provide an initial indication about the effectiveness of the NEVERMIND system and that more research will be needed in the future to validate and replicate the results of this study in specific categories of patients. However, if the NEVERMIND system will be effective in reducing depressive symptoms in patients with a severe somatic condition, the results of this study have future implications for a wide range of stakeholders including patients, physicians, and the healthcare system.

## Data Availability

Data sharing is not applicable to this article as no datasets were generated or analysed for developing the protocol. Investigators in the study have access to the current dataset as well as to the final trial dataset. There are no plans for granting public access to the full protocol, participant-level dataset, and statistical code. However, these can be made available upon request.

## Abbreviations

BDI-II: Beck Depression Inventory II
CBT: Cognitive Behavioural Therapy
CIASS: Chronic Illness Anticipated Stigma Scale
CM: Case Manager
DASS-21: Depression, Anxiety and Stress Scale
DMC: Data Monitoring Committee
ECG: Electrocardiography
eGFR: Estimated glomerular filtration rate (eGFR)
EU: European Union
HAM-D: Hamilton Rating Scale for Depression
HIV: Human Immunodeficiency Virus
ITT: Intention to treat
KDOQI: Kidney Disease Outcomes Quality Initiative
KI: Karolinska Institutet
LC: Levels of Care
MI: Myocardial Infarction
MNAR: Missing not at random
PSS: Paykel Rating Scale for Anxiety
QoL: Quality of Life
RAPA: Rapid Assessment of Physical Acitvity
TAU: Treatment as Usual
UPM: Universidad Politécnica de Madri
WHO-5: WHO Well-being Scale
